### Study design and setting

CLOCS-2 will use an observational retrospective case-control design to compare past purchase patterns of participants (men and women) with and without a cancer diagnosis using already existing data gathered by two major high street retailers, one of which is a health and beauty retailer (Boots), and the other a groceries and general merchandise retailer (Tesco). Furthermore, we will collect data on risk factors for the following cancers: oesophageal, stomach (gastric), colorectal (bowel), pancreatic, liver, bladder, endometrial, uterine sarcoma, ovarian and vulval.

CLOCS-2 is a secure online study delivered via Research Electronic Data Capture (REDCap), a web-based application designed to support data capture for research studies, providing secure data storage, audit trails and easy survey administration.^18^

The study documents, including the informed consent form, patient information sheet (PIS), and the health survey, are available in English, Gujarati and Polish. This represents an improvement over the original CLOCS study. Gujarati and Polish were selected as additional languages because they were the most commonly spoken within the relevant Research Delivery Networks (RDNs) and Primary Care Networks (PCNs) in the study area.

### Study timeline

CLOCS-2 study recruitment is planned to take place from 4 February 2026 until January 2028.

### Participants

#### Inclusion/exclusion criteria

The CLOCS-2 will recruit up to 2900 people for the study. This will comprise two participant groups: cases (n=1450) and controls (n=1450). The eligibility criteria for both participant groups (men and women) are that participants must be at least 18 years old, reside in the UK at the time of giving informed consent, and be registered with an NHS GP practice. Participants must own, or have a household member who owns, at least one participating high street retailer loyalty card to be eligible to join the CLOCS-2 case-control study. Finally, all participants must be able to provide written informed consent and willingness to comply with all required study activities (figure 1).

**Figure 1 F1:**
[figure not shown]
Cancer Loyalty Card Study-2 (CLOCS-2) recruitment and consent process. Overview of participant identification, invitation, eligibility screening and informed consent. GP, general practitioner; REDCap, Research Electronic Data Capture.

#### Eligibility for cases

Men and women diagnosed and living with an eligible cancer type within the 2 years prior to the recruitment date are eligible to join the CLOCS-2 case-control study as cases. Patients’ usual care will continue to be provided by their usual healthcare professionals, and CLOCS-2 participation does not exclude patients from participating in other clinical or non-clinical studies.

#### Eligibility for controls

Men and women who have not been diagnosed with any cancer in the last 6 years prior to recruitment (except where the diagnosis was non-melanoma skin cancer).

### Recruitment

The CLOCS-2 case-control study recruitment and consent process is outlined in figure 1 and described further below.

Participants (cases and controls) will be recruited across the UK through individual GP practices and Be Part of Research. Additional cases will be recruited through NHS cancer c*linics.*

#### GP practices

After submitting an expression of interest, new RDNs or PCNs will receive further study information and set up an organisation information document (OID) for each participating GP practice. The OID developed with the North London RDN will serve as a template for other networks. A brief site initiation visit (SIV) will be held with each new RDN/PCN conducted by the CLOCS-2 team.

Clinical team members at each GP practice will identify potential study participants with a primary diagnosis of one of the eligible cancers, received in the last 2 years prior to recruitment date. Eligible cases will be randomly selected if the number of potential participants exceeds the required size. GP practices will match invited cases with eligible controls based on age bracket, sex and the number of inhabitants. Controls will be randomly sampled from participants without a cancer diagnosis who meet the matching criteria, typically selecting one control per case. Once eligible participants are identified, the GP practice will send a text message (drafted by the CLOCS-2 team).

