## Study objectives

The primary objective of this case-control study is to identify the time points at which participants with the following cancers (cases): oesophageal, stomach (gastric), colorectal (bowel), pancreatic, liver, bladder, endometrial, uterine sarcoma, ovarian and vulval, show statistically significant differences in their purchasing behaviours compared with purchase behaviours of participants without a cancer diagnosis (controls) over the previous 6 years. For controls, the purchases included are those recorded from participant consent to the study, up to a maximum of 6 years prior. For cases, the purchases included are those recorded up to the date of cancer diagnosis, to a maximum of 6 years, depending on when the diagnosis occurred. These behaviours include the purchase of items suspected of being used for symptom management (eg, painkillers, indigestion tablets) as well as changes in the frequency or quantity of other items purchased leading up to diagnosis. Participants’ historic loyalty card data will be collected from two major high street retailers.

The secondary objectives of CLOCS-2 are to: (1) Define a purchase threshold that may act as an “alert” for potential cancer symptoms in individuals and assess the predictive value of purchasing behaviours in the early detection of these cancers, (2) Develop a predictive model to determine the accuracy and efficacy of these purchasing behaviours for early cancer detection and (3) Create risk profiles from the participants’ self-reported health data and incorporate these into the analyses.

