### Health survey

After completing consent, participants will be required to complete an online questionnaire (approximately 50 min) about their health, medical history and lifestyle (figure 2). The design of this questionnaire has been informed by our understanding of well-established cancer risk factors and symptoms reported by patients across the target cancers in previous research.^11^ Participants with a cancer diagnosis will also be asked to provide details on the cancer type (oesophageal, stomach (gastric), colorectal (bowel), pancreatic, liver, bladder, endometrial, uterine sarcoma, ovarian and vulval) and stage (I, II, III and IV) of cancer. We will use this information to inform risk assessment and to stratify loyalty card purchasing data for cases and controls by time of diagnosis. Purchasing patterns will then be examined by cancer type and stage at diagnoses.

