### Sample size and statistical power

A power calculation was conducted for the following four cancers: ovarian, pancreatic, oesophageal and colorectal. This calculation was based on the former CLOCS study^19^ which was conducted using conditional logistic regression of matched pairs. The calculation assumes an effect size of OR=1.38, with 80% power at alpha=0.05 and estimates n=223 case-control pairs are needed for each cancer type. To allow for attrition of ~10%, the total number we will aim to recruit for each of these four cancers will be 250 (n=1000). No power calculation has been done for the remaining six types of cancer as these are being piloted, but the aim is to recruit 75 participants per cancer.

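### Controls for ovarian, endometrial and uterine sarcoma cases need not have the organ at risk, so a matched comparator may be a woman who could not have become that case

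*Protocol article*

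**What the plan says.** The case types are "oesophageal, stomach (gastric), colorectal (bowel), pancreatic, liver, bladder, endometrial, uterine sarcoma, ovarian and vulval" (Study objectives). Three of them arise in an organ that a woman without cancer may have had removed: endometrial, uterine sarcoma and ovarian.

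The rules that decide who can be a control are these:

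- **GP practices, matching factors:** "GP practices will match invited cases with eligible controls based on age bracket, sex and the number of inhabitants".
- **Eligibility for controls:** "Men and women who have not been diagnosed with any cancer in the last 6 years prior to recruitment", with an exception for non-melanoma skin cancer.
- **Inclusion/exclusion criteria:** "participants must be at least 18 years old, reside in the UK at the time of giving informed consent", plus GP registration, a participating loyalty card in the household, and consent.
- **GP practices, the draw among those who qualify:** "Controls will be randomly sampled from participants without a cancer diagnosis who meet the matching criteria, typically selecting one control per case".
- **Be Part of Research:** volunteers are screened against the same inclusion and exclusion criteria.

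None of these mentions organ status, hysterectomy or removal of the ovaries.

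On the analysis side, Statistical methods plans conditional logistic regression repeated by cancer type, and an exploratory risk profile for each participant and cancer type, formed by summing risk factors. A secondary objective is to build risk profiles from "self-reported health data and incorporate these into the analyses". The Health survey asks participants "about their health, medical history and lifestyle", and the section on study risks and bias plans adjustment for self-reported comorbidities and GP visit frequency. Neither is described as a way of restricting controls to women at risk.

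**The concern.** Controls should represent the population from which the cases arose: a control is someone who would have been counted as a case had the disease developed. A woman without a uterus does not meet that test for endometrial cancer or uterine sarcoma, and a woman with both ovaries removed does not meet it for ovarian cancer. Random sampling within age bracket, sex and number of inhabitants lets both in. In a typical one-to-one pair she is then the only comparator for her case.

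Two results are at stake. The first is the cancer-specific purchase odds ratio, if women without the organ buy target items (pain remedies among them) at a different rate from women with it. The second is the cancer-specific risk profile, which would give a score for a cancer to women who are not at risk of it. Ovarian cancer is one of the four powered cancers and the one in which the finding to be validated was made.

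**Working it through.** **1. The plan's own figures.** The sample size section states: "The calculation assumes an effect size of OR=1.38, with 80% power at alpha=0.05 and estimates n=223 case-control pairs are needed for each cancer type". Allowing for about 10% attrition, 223 / 0.90 = 247.8, so 248, which the plan rounds to 250. The total is 4 × 250 + 6 × 75 = 1,450, the case target, so 250 and 75 count cases.

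The 223 cannot be rebuilt from the stated inputs alone. With a binary exposure and p = 1.38 / 2.38 = 0.580, McNemar's test (two-sided) needs (1.96 × 0.5 + 0.842 × √[p(1 − p)])² / (p − 0.5)² = 306 discordant pairs. With a continuous exposure per standard deviation, 2(1.96 + 0.842)² / (ln 1.38)² gives 152 pairs at zero within-pair correlation; 223 is reached only at a correlation of about 0.32, which is not stated. This point does not depend on how 223 was obtained. The power figures below simply take the plan's 80% at 223 pairs as given.

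**2. Control places under the rule.** At one control per case: 250 (ovarian) + 75 (endometrial) + 75 (uterine sarcoma) = 400.

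**3. If such controls are kept.** Assumptions, none of them in the documents: 30% of controls with the organ are exposed (p0 = 0.30); a share f of controls lacks the organ; r is the odds ratio of target purchase for control women without versus with the organ.

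- Cases: p1 = 1.38 p0 / (1 − p0 + 1.38 p0) = 0.414 / 1.114 = 0.372
- Controls without the organ: pr = r p0 / (1 − p0 + r p0)
- All controls: pm = (1 − f) p0 + f pr
- Observed odds ratio (crude, pairing ignored): [p1 / (1 − p1)] / [pm / (1 − pm)]
- Power: Φ(2.80 × ln(observed) / ln(1.38) − 1.96)

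Example with f = 10%, r = 2.0: pr = 0.60 / 1.30 = 0.462; pm = 0.270 + 0.046 = 0.316; observed odds ratio = 0.591 / 0.462 = 1.28.

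| r | Odds ratio (power), f = 10% | Odds ratio (power), f = 20% |
|---|---|---|
| 0.8 | 1.41 (85%) | 1.44 (89%) |
| 1.0 | 1.38 (80%) | 1.38 (80%) |
| 1.2 | 1.35 (75%) | 1.33 (70%) |
| 1.5 | 1.32 (68%) | 1.27 (54%) |
| 2.0 | 1.28 (57%) | 1.19 (32%) |

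Results are similar at 20% and 50% exposure. The direction depends entirely on r, and at r = 1 there is no bias. The gain in power when r is below 1 is no benefit, since it comes from an inflated odds ratio.

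**4. If they are found only after enrolment and their pairs dropped.** Ovarian pairs left = 250 × 0.90 × (1 − f); power = Φ(2.80 × √(pairs / 223) − 1.96).

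| f (assumed) | Pairs left | Power | Pairs to recruit to keep 223 |
|---|---|---|---|
| 5% | 214 | 78% | 261 |
| 10% | 202 | 76% | 276 |
| 20% | 180 | 71% | 310 |

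If organ status is checked when controls are selected, the sample size does not change.

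**5. Risk profiles.** No arithmetic is needed. A summed score per participant and cancer type, with no rule for a participant who lacks the organ, gives that woman a score for a cancer she is not at risk of, whatever the purchase data show.

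**The case against.** The strongest reply is that this is an omission in a condensed article: the full protocol may hold a fuller GP search specification, and organ status could still be applied when analysis pairs are formed. That has some force. But the article does set out control eligibility and the matching factors, and as stated they admit these women. Who is invited is settled at recruitment; an analysis plan can only drop or re-match them afterwards.

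A second reply is that the survey's medical history and the planned comorbidity adjustment deal with the matter. They could supply the information, but adjustment does not turn a woman who is not at risk into a valid comparator. It is fair to add that the risk profile is labelled exploratory and that two of the three cancers are unpowered pilots.

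The other side is right against several stronger readings that a reader might infer:

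- **That the odds ratio is biased towards the null.** This needs recent surgery and raised purchases. Women operated on before the 6-year window need not buy more and may buy less.
- **That the symptoms behind such surgery cannot occur in cases.** They can. An ovarian case may have had a hysterectomy with the ovaries kept.
- **That every such pair is invalid for the purchase analysis.** The odds ratio is distorted only if purchases differ by organ status.
- **That 10% to 25% of the 400, or 40 to 100 controls, are affected.** The documents give no such share. For the 250 ovarian places only removal of both ovaries counts, so one range cannot serve for uterus and ovary alike.

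Finally, purchase records carry no organ status, so an alert based on purchases alone would reach these women. Leaving them out of all threshold work could misstate false positives. That point stands and is taken into the fix.

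**Conclusion.** The concern holds as a defect in control selection for three cancer types. As the article fixes eligibility and matching, a woman who could not have become the case can be its matched comparator and can be scored for a cancer she is not at risk of. The risk-profile part follows directly from the text. The effect on the purchase odds ratio is possible but unquantified: the documents fix neither its size nor its direction. The illustrated range of 1.41 to 1.28 around a true 1.38 rests on assumed values of 30% exposure, 10% lacking the organ and purchase odds ratios of 0.8 to 2.0; large losses of power appear only towards the upper end of the assumed range. Up to 400 control places are open to the problem, and the share actually affected is unknown. It is worth correcting because correction at selection is cheap and correction after enrolment costs pairs.

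**What to change.** Take the index date as the end of the purchase window, which for controls is the date of consent. Add to the control criteria:

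- controls matched to endometrial or uterine sarcoma cases must have a uterus at the index date;
- controls matched to ovarian cases must have at least one ovary at the index date.

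Apply this through the GP record when controls are matched, and through a medical-history item in the survey for controls from Be Part of Research. The same item serves as a check on GP controls. Women who do not qualify can be controls for other cancers. For anyone already enrolled, re-match or prespecify an exclusion or sensitivity analysis. State that the cancer-specific risk profile is not calculated for a participant without the organ concerned.

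For the purchase-only alert threshold, also report performance with women without the organ included, because such an alert would reach them.

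The cost is one search filter, one survey item and slightly more screening per control. The sample size is unchanged if the rule is applied at selection.

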#### Be part of research

Be Part of Research is a UK-based participant recruitment service run by the National Institute for Health and Care Research, which is open to anyone living in the UK. Registered volunteers provide demographic and health information and can indicate the types of studies they are interested in. The platform then pre-screens individuals based on this information and their stated interests to identify those who may be eligible for specific studies. Individuals who meet these criteria may be contacted by email with information about the CLOCS-2. All respondents will undergo further screening against the study’s inclusion and exclusion criteria prior to enrolment.

#### NHS cancer clinics

Recruitment may also take place at NHS cancer clinics if we are unable to meet our recruitment target for cases. An OID will be created for each recruited clinic in the same way as the RDNs/PCNs. Capacity and capability will be sought from each cancer clinic, with an SIV held prior to recruitment. Cancer clinics will follow the same procedures as the GP practices, that is, identify potential study participants with a primary diagnosis of one of the eligible cancer types received in the last 24 months. As with GP practices, the only way a person can access our recruitment site is via a link received by a text message.

Eligible patients with a cancer diagnosis from one of the ten eligible cancers will be recruited by members of their healthcare teams at selected NHS trusts and hospitals across the UK that have agreed to approach patients at clinics. These healthcare teams will be registered as a research site and will have a principal investigator (PI) leading the recruitment to CLOCS-2. The PI and the research nurses will facilitate recruitment by identifying patients (cases) when they think it is suitable to approach patients with the study information to consider participation.

### Informed consent

Both cases and controls will need to complete a digital consent form to participate in the CLOCS-2. The consent form includes three sections. The first section details consent to take part in CLOCS-2. The second section is for participants to consent to the research team requesting their data from high street retailers as the registered keeper. The third section is optional and relates to participation in future research. Participants who are not the primary registered card holder but share the use of the loyalty card or live in a household where the primary cardholder makes purchases on their behalf are still eligible to take part in the study. However, to access their shared loyalty data, the primary registered cardholder must also register for the study. If the primary cardholder does not join the study, the CLOCS team will not request shopping data from the high street retailer and will use only the data from the health survey they completed.

All individual consents will be transferred from REDCap to the secure and encrypted server within Imperial College London’s Certified Secure Research Environment (CSRE), formerly known as the ‘Secure Enclave’, once study recruitment is complete. Participant loyalty card details will be entered into a comma-separated values (CSV) file and encrypted for secure data requests from retailers using a secure file transfer protocol. After recruitment is finished and all transfers are complete, individual consent forms will be permanently deleted from REDCap.

### Data sources and variables

#### Loyalty card data (for cases and controls)

CLOCS-2 participants or someone in their household will hold a loyalty card at one or both participating retailers that can be accessed by the UK population within all precincts, allowing the study to assess purchases of over-the-counter medications (ie, painkillers and indigestion medications) and eating habits. Eating habits will be used to identify dietary risk factors for specific cancers and to examine changes in dietary behaviour in response to potential cancer symptoms. The study will not include prescription-based pharmacy data which are not recorded in loyalty cards. After participants have provided consent, the CLOCS-2 team or the participant through the retailers’ OpenID platform (an interoperable authentication protocol that simplifies the way to verify the identity of users) will request their loyalty card data from the retailer, which will include individuals’ past purchase records from up to 6 years prior to the relevant cut-off date (study consent for controls or date of cancer diagnosis for cases). The purchase data will include each individual purchase, date of purchase, the location (ie, store postcode) and the product categorisation that is provided by the retailers. No additional individual information will be requested from the retailers.

### Health survey

After completing consent, participants will be required to complete an online questionnaire (approximately 50 min) about their health, medical history and lifestyle (figure 2). The design of this questionnaire has been informed by our understanding of well-established cancer risk factors and symptoms reported by patients across the target cancers in previous research.^11^ Participants with a cancer diagnosis will also be asked to provide details on the cancer type (oesophageal, stomach (gastric), colorectal (bowel), pancreatic, liver, bladder, endometrial, uterine sarcoma, ovarian and vulval) and stage (I, II, III and IV) of cancer. We will use this information to inform risk assessment and to stratify loyalty card purchasing data for cases and controls by time of diagnosis. Purchasing patterns will then be examined by cancer type and stage at diagnoses.

**Figure 2 F2:**
[figure not shown]
CLOCS-2 questionnaire flow following informed consent. Flow diagram showing the sequence of the online questionnaire completed after consent including sections on health status, medical history and lifestyle factors and the approximate duration of each section. CLOCS-2, Cancer Loyalty Card Study-2.

### Data extraction from the high street retailers

For both high street retailers, we will request up to 6 years in total of back-dated purchase data. The exact amount of data available for each participant will depend on how long they have had their loyalty card. Following participant consent, this data will be backdated from the date of study consent for controls or from the date of cancer diagnosis for cases.

The process for requesting data will differ between the two participating high street retailers. For Tesco, we will also use their Open ID Connect platform (figure 3). To facilitate this, a custom landing page was built which directs participants from REDCap to the retailer’s OpenID platform where participants will be able to sign in using their store login details. This ensures the retailer receives direct consent from the participants to share their loyalty card data with the CLOCS-2 research team. This approach eliminates the need for manual identity verification (eg, uploading ID documents), which was a barrier in the original CLOCS. It streamlines the process, reduces participant burden and improves data security by allowing the retailer to authenticate participants directly. It also ensures compliance with the retailer policies for sharing purchase data with third parties.

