### Statistical methods

We will use descriptive statistics to provide details on the characteristics of cases and controls by sociodemographic (eg, age, sex and ethnicity), cancer type and by risk factors.^11^ We will report feasibility factors, including the number of participants with a loyalty card from either participating retailer, the number with cards from both retailers and the number of years of data available for analysis.

We will aim to define the time by which cases and controls become statistically significantly different in their purchase behaviours using a multivariable, conditional logistic regression model with cancer as the outcome and ‘purchase proportion’ at different timepoints to diagnosis as the exposure, adjusting for potentially confounding variables. This analysis will be repeated and stratified by cancer type, stage at diagnosis and sociodemographic factors. Analyses will be performed for different types of medications and cancers separately and combined.

We will compare proportions using Fisher’s exact tests comparing target (items suspected to be used to treat cancer symptoms) and non-target (all other items) purchases. These comparisons will be made between cases and controls at each month prior to diagnosis. For controls, the reference will be the average monthly proportions of purchases across the observation period. Target items for analysis will include, but will not be limited to, medications for pain, indigestion, bloating relief and fatigue, along with other items commonly used to alleviate cancer-related and non-specific symptoms.^11^

We will conduct exploratory analyses to establish a potential risk profile for each participant and cancer type. This will be defined as a mathematical summation of all relevant risk factors, based on the published literature.^11^ In line with the findings from the original CLOCS, this analysis will be exploratory.^19^ Furthermore, we will investigate additional methods that leverage autocorrelation in the longitudinal data. Specifically, we will examine the evolution of individual purchasing frequencies and purchase trajectories to identify patterns—such as increases in purchases prior to diagnosis or distinct purchase peaks—that may be indicative or predictive of disease onset and time to onset.

All analyses will be done using statistical software R.

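### Fewer people are observed the further back from diagnosis, yet month-by-month case values are set against a whole-period control average and read as a time of divergence

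*Protocol article*

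**What the plan says.** The Protocol article treats six years as a ceiling. Under Data extraction from the high street retailers it says "we will request up to 6 years in total of back-dated purchase data", and then "The exact amount of data available for each participant will depend on how long they have had their loyalty card".

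The date from which history is counted back differs by group. Study objectives says "For controls, the purchases included are those recorded from participant consent to the study, up to a maximum of 6 years prior". For cases the record stops at diagnosis and extends back "to a maximum of 6 years, depending on when the diagnosis occurred". Eligibility for cases admits people "diagnosed and living with an eligible cancer type within the 2 years prior to the recruitment date". The criteria under Participants ask for a card held by the participant or a household member, and name no card age.

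The primary objective is to find the time points at which cases "show statistically significant differences in their purchasing behaviours compared with purchase behaviours of participants without a cancer diagnosis (controls) over the previous 6 years". Statistical methods plans conditional logistic regression on the purchase proportion at different times before diagnosis, and Fisher's exact tests of target against non-target purchases. Of the tests it says "These comparisons will be made between cases and controls at each month prior to diagnosis", and directly afterwards "For controls, the reference will be the average monthly proportions of purchases across the observation period". The number of years of data available is to be reported as a feasibility item.

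**The concern.** Someone whose card was open at a given lag was also holding it at every shorter lag. Going back in time, the observed group can therefore only lose members. Near months hold nearly everyone, and far months hold only people with old cards.

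The primary output is a point in time, so this matters in two ways.

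- **Composition.** A far-month case value comes from long-standing card holders only, while the control reference averages over controls of every card age. If the two kinds of holder buy target items at different rates, the case curve moves relative to a flat control line as newer holders enter, with no cancer effect at all.
- **Precision.** With fewer observed pairs at long lags, significance is harder to reach there. The earliest significant month then partly reflects how old the cards are. That month would feed the alert threshold named in the secondary objectives.

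**Working it through.** **1. The plan's own figure.** Sample size and statistical power gives 223 pairs per main cancer for OR 1.38, 80% power and alpha 0.05. These three inputs alone do not determine 223. A matched-pair formula with a binary exposure needs 306 discordant pairs (two-sided). A continuous exposure, with the OR per standard deviation, needs 152 pairs, and reaches about 223 only with an unstated within-pair correlation or R-squared near 0.32. So 223 is neither confirmed nor refuted, and serves here only as an anchor. The later steps agree: 223/0.9 = 248, against 250 recruited, and 4 × 250 + 6 × 75 = 1,450.

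**2. Pairs observed at lag k.** Assumptions, none of them in the documents: card age T at consent is uniform on 0 to 72/s months, where s is the share of cards under six years old; time from diagnosis to consent is uniform on 0 to 24 months (mean 12); card ages are independent within pairs; one card per person.

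- Control coverage = 1 − k/(72/s)
- Case coverage = 1 − (k + 12)/(72/s)
- Pairs = 223 × case coverage × control coverage
- Power = Φ(2.80 × √(pairs/223) − 1.96), which returns 80% at 223 pairs

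| s | Lag (months) | Cases | Controls | Pairs | Power |
|---|---|---|---|---|---|
| 10% | 60 | 0.90 | 0.917 | 184 | 72% |
| 30% | 36 | 0.80 | 0.85 | 152 | 64% |
| 30% | 60 | 0.70 | 0.75 | 117 | 53% |
| 30% | 72 | 0.65 | 0.70 | 101 | 47% |
| 50% | 60 | 0.50 | 0.583 | 65 | 33% |

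Starting from all 250 recruited pairs with no other attrition, the 30% row at 60 months becomes 250 × 0.525 = 131 pairs, about 57%. Keeping 223 of 250 pairs needs 223/250 = 89.2% of pairs covered, or √0.892 = 94.4% of individuals.

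**3. The same model at 9 months,** where the Introduction places OR 1.38. From 250 pairs, power is 83%, 79% and 76% for s = 10%, 30% and 50%. The loss is modest there and falls mainly on long lags.

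**4. Composition, with no cancer effect.** Assume that half of people have 72 months of history and buy target items at 3%, and half have 36 months and buy at 4%.

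- Recent case months: 0.5 × 3% + 0.5 × 4% = 3.5%. Far case months: 3.0%.
- Control average over person-months: (36 × 3% + 18 × 4%)/54 = 3.33%. The OR is 1.05 in recent months and 0.90 in far months.
- Control average taken per person and then across people: 3.5%. The OR is 1.00 in recent months and (0.03/0.97)/(0.035/0.965) = 0.85 in far months.

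Under either reference the case odds rise by a factor of 0.03627/0.03093 = 1.17 towards diagnosis. With 80% long histories, the person-month ORs are 1.03 and 0.96. With equal rates both are 1.00.

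**5. Retailer mix.** One retailer sells health and beauty goods, the other groceries, and a participant may hold either card or both. If the two cards were opened at different times, the target share can change with lag within one person.

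**The case against.** The case on the other side is substantial, and much of it stands.

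- **Disclosure.** The article says throughout that six years is a maximum, states that data length varies, and will report years available. A reader might infer that the plan assumes constant coverage, but no sentence says so. Rules for unobserved months or minimum history may sit in a fuller document, and their absence here is no error. What remains is what the text does fix: a whole-period control average set against month-specific case values.
- **The model.** In 1:1 conditional logistic regression, a pair with one member unobserved drops out. Unequal coverage does not in itself bias that comparison. The effect there is lost precision and a changing population of pairs.
- **The pair counts.** These describe same-lag paired comparisons and not the Fisher tests, where a control need not be observed at the lag in question. On case coverage alone, the 30% scenario at 60 months leaves 0.70 × 223 = 156, not 117.
- **Proportions.** The exposure is a share of purchases, so months before a card was opened create no false zeros.
- **Fewer cases at every lag.** A reader might infer this from the different starting dates. It does not follow: if every card were over eight years old and retailers supplied six years before diagnosis, both groups would be fully covered.

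**Conclusion.** The point holds in a limited form. As written, the set of people behind each monthly case value changes with lag while the control reference does not. A time of divergence read across six years therefore mixes purchasing behaviour with card age.

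The loss of pairs at long lags needs only that some cards are too young to reach that far back. Its size rests on the assumed card-age distribution: 184 to 65 of 223 pairs at 60 months as the share of cards under six years old runs from 10% to 50%.

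A reader might infer that the results will be biased. The documents do not support that. Bias requires card age or retailer mix to be related to target purchasing, no figure is given for either link, and the direction is unknown. A reader might also infer that the study is underpowered. That does not follow either: the low power figures apply OR 1.38 at 60 to 72 months, where the article does not claim such an effect, and at 9 months little is lost.

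**What to change.** Change the analysis wording as follows.

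1. Start each person's observed window at the first recorded transaction, separately for each retailer card, and treat earlier months as unobserved. Purchase dates are already among the data requested.
2. Compare cases and controls at the same lag, within pairs where both members are observed, in place of the whole-period control average.
3. Report the number of observed pairs at every lag.
4. Keep the six-year analysis on all available pairs, so the stated objective is unchanged. Support the statement on when purchases diverge with a repeat on a fixed set of pairs observed throughout a stated common window.
5. Do not interpret the absence of a difference at lags with few pairs.
6. State that the 80% power refers to lags with at least 223 observed pairs.

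The cost is some extra analysis and reporting, with no new data. The fixed-set estimates will be less precise and will describe longer-standing card holders, which is why they support the full analysis and do not replace it.
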